### 6.3 Analysis groups

- All randomized patients (All randomized patients, including those lost to follow-up.)
- Full analysis set (All patients which were randomized and treated.)
- Complete case set (All data present at both baseline and control)

## 7. Trial sample

### 7.1 Screening data, eligibility and recruitment

The total number of included patients and reasons for non-completion will be summarized and tabulated. A trial profile flow diagram will be used to summarize the number of patients who were:

- Included at initial evaluation
- Eligible at initial evaluation and underwent installation of tympanostomy tubes.
- Received randomized allocation.

- Lost to follow-up.
- Randomized and included in primary analysis.
- Randomized and excluded from primary analysis.

## 7.2 Withdrawal/Follow-up

The status of eligible and randomized patients at trial end will be tabulated by treatment group according to whether they:

- Completed intervention but not assessments
- Withdrew consent.

## 7.3 Baseline patient characteristics

The patient demographics include age, gender, height, weight, tobacco use in the home, the educational, guardianship and work status of the parents/guardians. The patient demographics will be summarized and presented using descriptive statistics (N, mean, standard deviation, median) for continuous variables, and number and percentages of patients for categorical variables as appropriate.

# 8. Analysis

## 8.1 Analysis of the primary efficacy endpoint

### 8.1.1 Pure tone average (PTA)

The primary outcome will be the mean change in PTA from baseline between those patients controlled by their general practitioner and those controlled through the specialist health care system. PTA will be measured by taking the mean of the hearing thresholds in dB measured at 500Hz, 1kHz, 2kHz and 4kHz using pure tone audiometry.

### 8.1.2 Statistical analysis

Analyses will be performed according to intention to-treat. Mean +/- SD and summary statistics appropriate for the distribution will be reported for the primary outcome and each of the key secondary outcomes. A linear mixed model (LMM), with the combination of time and treatment as fixed factors (with three levels; 'baseline', 'post-ENT' and 'post-GP') and participant ID as random factor, will be applied to compare mean PTA 2 years after. We will also perform a t-test to compare the mean change in PTA after 2 years between GP controlled patients and those controlled within the specialist health care system.

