### **Materials and Methods**

The parents of children are invited to participate in the study upon their outpatient appointment for assessment to drain insertion. They receive written information including the point of the study. The study additionally requires an audiological consultation with either an audiographer or doctor at the hospital before the operation as well as one at 2 and 4 years postoperatively. In addition to this they will be required to fill out questionnaires at all three timepoints. Self-reporting forms will contain amongst other things the validated OM 8-30 questionnaire which aims to broadly describe children's ear complaints and situation over the last 3 months (16). In addition to this quality of life will be recorded using The Pediatric Quality of Life (PedsQL) where we will use the parent reported forms for children dependent on how old they are (forms can be found for 2-4 year olds, 5-7 year olds and 8-12 year olds)(17, 18) and the Strengths and Difficulties Questionnaire's Norwegian version (SDQ-Nor)(19). Previous audiological information will be collected from the journal system for example preoperative hearing and dates for previous drain insertions.

In the qualitative part of this study an individual semi-structured interview will be conducted of a choice of guardians from both follow-up groups from up-to 3 timepoints; within the first 14 days, 6 and 24 months after drain insertion.

Data from NPR and KUHR/KPR will be collected for the health economic analyses (see examinations and measurements page 7)

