### **Number of participants**

The calculation of the number of participants was performed by the statistician. The number depends on which factors which are to be analyzed and which statistical method will be used. We are interested in determining differences in effect of treatment in disfavor of the GP-group, but a better result in this group would be optimal in regards to the clinical implications (performing therefore a two sided test. No difference between groups is also a possibility and of interest (equivalence study). With a focus on the likeness between groups it is especially important to avoid falsely concluding “no effect” (type II error), which implies that we want a high power for the test for difference between groups, minimum 90%, preferably up to 95%.

The primary end-point is hearing, which is measured in dB (continuous variable). We examine changes in average hearing in the frequencies 0,25-4,0 kHz between 2 timepoints. The smallest clinically relevant change in hearing is 5dB. With an expected bettering of 10dB in the one group and 5dB in the other group (absolute diff. 5dB), and estimated standard deviation of 10dB in each group, we would with a significance of 5% need 85 (105) participants in each group to determine a difference with 90% (95%) power. To account for skew from the normal distribution, at least 15% should be added (increase to 98 or 131 in each group) and an additional 20% for drop-outs. A minimum of at least 118(157) participants in each group would be required. To maintain power in a model where we account for study center (random factor), and other clinical or demographic factors, the number must be increased (by at least 10 cases per variable. The total is now increased from 314 to 400, 200 participants in each group due to multiple participating hospitals.

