### **Statistical analysis**

Linear mixed model (LMM) with center as random factor will be used to examine if there is a significant long-term effect (at 2 and 4 years) of treatment (insertion of drain) on hearing level and other audiological and clinical factors. Interaction joints will be included in the statistical model to examine the effect of treatment, measured in the form of change compared to pre-operative measurements, is the difference between patients who receive

follow-up through their GP or hospital. Log transformation of data will be actual if it is relevant to study relative over absolute changes, and transformation of data will be actual if a response variable appears to be skewed. Alternative non-parametric models can be used as needed.

Differences between the two randomization groups (hospital, GP) taking into account severity of complications, number of reoperations and proportion of re-referrals under the follow up period will be examined with the help of chi-squared tests (as a categorical variable) or Mann-Whitney test of differences of the entirety. It will also be actual to compare groups taking into account re-operation rate, and identify riskfactors for recurrence (re-operation), by using different types of survival analysis models, alternatively a logistic regression (if one can not account for time for re-operation).

If there is no significant difference between groups, we will focus on magnitude of differences between groups. With a lack of significant difference we will use a 95% confidence interval for absolute difference around 0 (around 1 for relative difference), but border values in the interval must be less than that which is considered a clinical difference of significance. What these values are will depend on which factors are being analyzed.

The health economic analyses will be performed based on randomization and where follow up has been performed.

In the qualitative portion of the study the transcription of interviews will be done continuously. Multiple researchers belonging to the research group and the project will collaborate to read and analyze the transcript. The analysis method will be adjusted to the data and presented problems.

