### 5.3 Sample size

The sample size was calculated prior to inclusion by a statistician. Hearing thresholds are determined in 5 dB steps and equality in PTA 2 years after surgery (primary endpoint) was

therefore defined as  $< 5$  dB (5 dB as equivalence margin). To avoid an incorrect conclusion of ‘no difference’ between the groups (type II error), the power of the tests for detecting a difference of  $\geq 5$  dB must be high ( $\geq 95\%$ , error margin  $< 5\%$ ). Thus, with a power of 95% and a significance level of 5% (two-sided test), 105 participants are needed in each group to be able to detect an absolute difference in mean PTA between the groups of  $\geq 5$  dB (SD 10 dB) in each group based on the results of our previous study. 15% was added to mitigate a potential skew distribution of hearing level, and an additional 20% to account for potential dropouts, we are left with a sample size of 145 participants in each group. To maintain power in an analysis stratified for six study centers (five additional parameters in model), the total sample size must be increased by at least 50 participants, applying the general rule of thumb of at least 10 cases per parameter. If we assume that the 50 participants are evenly distributed in the two randomization groups, this leaves us with a sample size of at least 170 participants in each group. We initially planned to truncate up to 200 participants in each group to maintain power in case of a higher dropout rate. However, during the pandemic the surgery rate in Norway dropped dramatically, and with it our inclusion rate. After a preliminary assessment of our drop-out rate and recalculation by the project’s statistician, it was determined that 135 participants in each group would be sufficient.

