## 8.2 Subgroup analyses

Subgroup analysis of the primary endpoint will be conducted for age, gender and severity of hearing loss at inclusion. The groups will be divided into thirds for analysis. Both the complete case set, and the two randomized groups will be divided into thirds according to level of hearing loss or age before subsequent analysis.

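### The primary model adjusts for no clinical or demographic factor; prespecifying age, and previous drain insertion with a missing-value rule, would bring a small precision gain at little cost

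*Combined protocol and SAP*

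**What the plan says.** **Protocol, Number of participants.** The sample is enlarged to keep power "in a model where we account for study center (random factor), and other clinical or demographic factors". The allowance is at least ten cases per variable. The factors beyond centre are not named, and the increase from 314 to 400 is attributed to the number of hospitals.

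**Protocol, Statistical analysis.** "Linear mixed model (LMM) with center as random factor will be used". No patient-level covariate is named.

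**SAP 8.1.2.** The model is built "with the combination of time and treatment as fixed factors", a single three-level factor (a baseline level shared by both arms, then one post-operative level per arm), with "participant ID as random factor". A t-test on the change in pure tone average (PTA) is added. Neither analysis has a clinical or demographic term.

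**What is recorded.** SAP 7.3 lists age among the baseline characteristics. SAP 8.2 states: "Subgroup analysis of the primary endpoint will be conducted for age, gender and severity of hearing loss at inclusion". The protocol's Materials and Methods section gives "preoperative hearing and dates for previous drain insertions" as examples of information taken from the hospital journal. Previous drain insertion is not in the SAP's baseline list and enters none of its analyses.

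**The concern.** Prespecified baseline covariates leave a randomised comparison valid. If they predict the outcome, they also narrow its interval. Age at operation and previous drain insertion are plausible predictors of 2-year hearing in children aged 3–10, and the trial plans to collect both anyway.

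Precision has some value here. The plan was reduced from 200 to 135 per group, and the result is read from a two-sided 95% interval against a 5 dB margin. If covariates are to be used, they must also be named before the data are unblinded; otherwise any later adjustment is open to the charge of selection.

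**Working it through.** **Inputs from the documents (SAP 5.3 and 6.1).** Margin 5 dB; SD 10 dB per group; two-sided 5% level; 95% power; 105 per group before inflation; 15% added for skewness; 20% added for dropout; final target 135 per group; two-sided 95% intervals.

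**Assumptions not in the documents.** (a) 108 evaluable per arm, that is 135 × 0.80. (b) R², the share of variance that age and previous drains explain, varied from 0 to 15%.

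**Step 1. Reproduce the plan's own figures.** n per group = 2(z₀.₉₇₅ + z_power)² × SD²/Δ².
- 95% power: 2 × (1.960 + 1.645)² × 100/25 = 104, against 105 stated.
- 90% power: 2 × (1.960 + 1.282)² × 100/25 = 84.06, rounded up to 85, as the protocol states.
- Inflation: 105 × 1.15 × 1.20 = 144.9, or 145; adding 25 per group for centre gives 170. Both match SAP 5.3.

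**Step 2. Simple calculation with covariates.** SE = 10 × √(2/108) × √(1 − R²). Half-width = 1.96 × SE. Power at no true difference = Φ(5/SE − 1.96).

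| R² | SE (dB) | Half-width (dB) | Power, true difference 0 |
|---|---|---|---|
| 0 | 1.361 | 2.67 | 95.7% |
| 5% | 1.326 | 2.60 | 96.5% |
| 10% | 1.291 | 2.53 | 97.2% |
| 15% | 1.255 | 2.46 | 97.9% |

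If GP follow-up were truly 1 dB worse (a further assumption), power = Φ(4/SE − 1.96): 83.6% at R² = 0, 85.4% at 5%, 87.3% at 10% and 89.0% at 15%.

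**Step 3. Allow for baseline PTA.** Step 2 applies R² to the full 10 dB SD. The SAP's model already carries baseline PTA through the shared baseline level, and baseline PTA may hold part of the same information. The SAP's model was therefore simulated with 108 per arm, SD 10 dB at each time, residual correlation 0.3 (assumed), 1,500 trials per scenario, and one covariate explaining 9% of the 2-year variance. Average half-width reported by the model:

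| The covariate predicts | No covariate | Main effect only | With covariate × time |
|---|---|---|---|
| Baseline and 2-year PTA equally | 2.48 | 2.42 | 2.43 |
| 2-year PTA, and baseline only weakly | 2.53 | 2.50 | 2.48 |
| 2-year PTA only | 2.55 | 2.54 | 2.49 |

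The reported interval narrows by about 0.5% to 2.5%. In the third row a main effect alone gains almost nothing, which is why the covariate needs its own effect at 2 years. In that row the spread of the estimates across trials, expressed as 1.96 × SD, fell further, from 2.57 to 2.43 dB (about 5%). The gain is small by either measure.

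**The case against.** The case for leaving the model alone is strong, and most of it stands.

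- **No commitment was broken.** A reader might infer that the SAP dropped an adjustment the protocol had promised. The protocol's wording is a sample-size remark with no factor named, its analysis section names only centre, and SAP 5.3 budgets parameters only for centre. Age and previous drains are this review's choice.
- **Age is not ignored.** It is summarised at baseline and used for subgroups. Nor does its use as a subgroup show that it predicts 2-year PTA: a subgroup analysis asks whether the follow-up effect varies with age, which is a different question.
- **Previous-drain data may be incomplete.** They are mentioned as an example of journal information, and completeness is not stated. Adding the variable without a missing-value rule could remove children from the analysis.
- **The gain is uncertain.** A reader might infer that the interval is certainly wider than it need be. No document gives either variable's prognostic strength beyond baseline PTA, and at R² = 0 nothing is gained.
- **The conclusion is unlikely to turn on it.** With 108 per arm, power at no true difference is already 95.7%. The 84% figure depends on a 1 dB deficit that no document specifies. The step up to 200 per group was a cushion against dropout.

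What remains against the objection is narrow. The adjustment is cheap, it is valid if fixed in advance, and the SAP does not say why the factors foreseen in the protocol were left out.

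**Conclusion.** The point holds as an optional, small improvement in precision. It is not an error, and it does not put the unadjusted comparison in doubt.

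With 108 evaluable per arm and an SD of 10 dB, the simple calculation gives a gain of zero at R² = 0, 0.07 dB at 5% (2.67 − 2.60) and 0.21 dB at 15% (2.67 − 2.46), against a 5 dB margin. These R² values are assumptions, and the upper figure is an optimistic case. With baseline PTA in the model, and a covariate explaining 9% of the 2-year variance, the interval the model reports narrows by about 0.5–2.5%.

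The documents do not support the stronger readings that a promised adjustment was abandoned or that the trial lacks power without it. Centre is the firmer discrepancy between protocol and SAP. It is named in the protocol's analysis section, it stratifies the randomisation, and SAP 5.3 allows for it ("To maintain power in an analysis stratified for six study centers (five additional parameters in model"), yet it is absent from SAP 8.1.2. That is a separate point, compatible with this one.

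**What to change.** Amend SAP 8.1.2 before allocation codes are linked:

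1. Add age at operation (continuous) to the primary mixed model, with a covariate × time term so that it has its own effect at 2 years.
2. Add previous drain insertion (yes/no) in the same way, with a stated rule for missing values so that no child is dropped. A separate category for not recorded would do this without conflicting with the no-imputation statement in SAP 8.1.3.
3. Keep the model as now written as a sensitivity analysis.

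If the trial team prefers not to adjust, one sentence explaining why the factors foreseen in the protocol were left out would close the gap.

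Cost: a few degrees of freedom and the missing-covariate rule, with no data beyond what the protocol already plans to collect. Restoring centre to the model can be done in the same amendment.

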### 5.2 Randomization

The randomization procedure is computerized and carried out utilizing the “WebCRF” software developed at the Unit for Applied Clinical Research at The Faculty of Medicine and Health Sciences, NTNU. The design is block randomization with blocks of varying sizes, with an allocation ratio of 1:1, stratified on the study center.

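### The SAP's mixed model and t-test leave out study centre, the stratification factor that the protocol's model includes; the loss is a slightly wide interval, not bias.

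*Combined protocol and SAP*

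**What the plan says.** Four places in the documents bear on centre.

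- **Allocation.** The protocol (Randomization) uses blocks with centre as stratum. SAP 5.2 confirms block randomisation "with an allocation ratio of 1:1, stratified on the study center".
- **Protocol model.** Protocol, Statistical analysis: "Linear mixed model (LMM) with center as random factor will be used". The protocol's section on number of participants also raises the sample size for a model with centre as a random factor.
- **SAP sample size.** SAP 5.3 starts from 105 per group, allows for skewness and drop-out to reach 145, and then adds at least 50 in total: "To maintain power in an analysis stratified for six study centers (five additional parameters in model"). The result is at least 170 per group. The target was later cut to 135 per group after a recalculation that is not shown.
- **SAP analysis.** SAP 8.1.2 gives a linear mixed model with one fixed factor at three levels (baseline, post-ENT, post-GP) and "participant ID as random factor, will be applied to compare mean PTA 2 years after", plus a t-test on the change in PTA. Neither has a centre term.

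No other section of the SAP brings centre into these analyses or says why it was dropped.

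**The concern.** The analysis as written matches neither the randomisation nor the protocol's own model nor the reasoning behind the planned 170 per group. A reader holding the trial's documents could defend two different mixed models, one with centre and one without.

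There is also a small statistical cost. Blocking within centre removes centre differences from the comparison of groups, but an analysis without centre still counts them as error. The participant effect does not stand in for centre: it absorbs centre variation into the between-participant variance, and the group comparison is made between participants. If centres differ, the reported interval is a little wider than it need be. That makes non-inferiority slightly harder to show, and it also makes a true disadvantage of GP follow-up slightly harder to detect. SAP 5.3 names a false conclusion of no difference as the error to avoid.

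**Working it through.** **1. The plan's own figure.** SAP 5.3 takes a 5 dB difference, SD 10 dB, two-sided 5% and 95% power.

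- The exact two-sample t calculation gives 104.93, so 105 per group, as stated.
- Skewness and drop-out: 105 × 1.15 × 1.20 = 144.9, so 145.
- Centre: 5 parameters × 10 cases = 50 in total, so 145 + 25 = 170 per group.

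The chain reproduces, and its last step is for centre alone. The final 135 is below even the 145 that precedes that step, so it cannot be told whether any allowance for centre survives in it.

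**2. Assumptions.** The documents give neither a centre variance nor a correlation between visits. I assume:

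- n = 108 analysed per arm (135 × 0.80, applying the SAP's 20% drop-out figure to the final target);
- total SD σ = 10 dB at a visit;
- ρ, the share of PTA variance due to centre, 0.02 to 0.10;
- r, the correlation between baseline and 2 years within a centre, 0.3 to 0.5;
- 1:1 balance within centre.

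**3. Mixed model, centre differences constant over time.** The three-level factor gives both groups one baseline mean, so with the participant effect the model largely adjusts for baseline. In large samples the variance of the group contrast is:

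- centre omitted: σ²(1 − R²)(2/n), where R = ρ + (1 − ρ)r is the correlation that the model sees;
- centre included: σ²(1 − ρ)(1 − r²)(2/n).

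The ratio of interval widths is √[(1 − R²) / ((1 − ρ)(1 − r²))]. The half-width is 1.96 × 10 × √(2/108) = 2.67 dB, times √(1 − R²) or √[(1 − ρ)(1 − r²)].

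| ρ | r | R | 1 − R² | (1 − ρ)(1 − r²) | Width ratio | Half-width without / with centre (dB) |
|---|---|---|---|---|---|---|
| 0.02 | 0.3 | 0.314 | 0.9014 | 0.8918 | 1.005 | 2.53 / 2.52 |
| 0.02 | 0.5 | 0.510 | 0.7399 | 0.7350 | 1.003 | 2.29 / 2.29 |
| 0.05 | 0.3 | 0.335 | 0.8878 | 0.8645 | 1.013 | 2.51 / 2.48 |
| 0.05 | 0.5 | 0.525 | 0.7244 | 0.7125 | 1.008 | 2.27 / 2.25 |
| 0.10 | 0.3 | 0.370 | 0.8631 | 0.8190 | 1.027 | 2.48 / 2.41 |
| 0.10 | 0.5 | 0.550 | 0.6975 | 0.6750 | 1.017 | 2.23 / 2.19 |

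The excess width is 0.3% to 2.7%, or about 0.01 to 0.06 dB.

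**4. t-test, centre differences constant over time.** A constant offset is subtracted out of each child's change. The width ratio is 1.00.

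**5. t-test, centres differing only at 2 years.** Take within-centre variance σ²(1 − ρ) at both visits. The change then has within-centre variance 2σ²(1 − ρ)(1 − r), and centre adds σ²ρ. The width ratio is √[1 + ρ / (2(1 − ρ)(1 − r))].

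- ρ = 0.02, r = 0.3: √(1 + 0.02/1.372) = 1.007.
- ρ = 0.10, r = 0.5: √(1 + 0.10/0.90) = 1.054.

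The t-test interval is about 1% to 5% too wide.

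**6. Mixed model, centres differing only at 2 years.** A centre main effect shifts both visits equally and so misses most of such a difference. Simulation under the same assumptions gives a gain of at most 0.8% (0.02 dB). Capturing it needs a centre-by-time term.

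**The case against.** The strongest reply is that this hardly matters. The error is conservative: with allocation balanced within centre, the estimate is unbiased and type I error does not rise above 5%. A change of at most 0.06 dB in the mixed-model limit, set against a 5 dB margin, is unlikely to alter the conclusion. All of that stands, and it limits the point to a modest one.

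A reader might infer a larger loss from the usual factor 1/√(1 − ρ), which gives 1.010 to 1.054 for ρ of 0.02 to 0.10, or up to about 0.14 dB on 2.67 dB. That factor describes a single follow-up value analysed without baseline. Neither planned analysis is of that kind: the t-test is on change, and the mixed model uses both visits. Differences in testers or setting that persist over time cancel in the first and are partly absorbed in the second.

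The sponsor could also cite the protocol's assumption that centres differ little demographically. The protocol uses it to justify not adding participants per centre for categorical variables. For PTA, both documents did add participants for centre.

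**Conclusion.** The inconsistency is certain: centre is in the allocation, the protocol's model and the justification of 170 per group, but not in SAP 8.1.2. Its statistical effect is small and conservative. Under the assumptions above, the mixed-model interval is about 0.3-2.7% too wide if centre differences are stable, with no effect on the t-test; the t-test interval is about 1-5% too wide if centres differ only at 2 years. If centres do not differ, nothing is lost.

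Two stronger readings go beyond the documents. One is that the trial recruited extra children for an adjustment it will not make; the allowance is documented only for the superseded 170, and how 135 was reached is not shown. The other is that centre was dropped in response to data. The SAP is dated October 2023, after 2-year visits were due to begin in autumn 2019, but it also keeps the group codes hidden until the analysis is complete (SAP 5.5), and nothing in it gives a reason for the omission. The case for the change is that it is nearly free and brings the documents into agreement.

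**What to change.** In SAP 8.1.2, add centre to the mixed model. Five fixed indicators would match SAP 5.3; a random factor would match the protocol. Either repairs the inconsistency, and with allocation balanced within centre the choice barely affects the group contrast. The SAP should say which is used and, if it departs from the protocol, why. Add centre-by-time if differences between centres at follow-up are to be captured.

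Replace or supplement the t-test with a linear model of 2-year PTA on group, baseline PTA and centre.

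If the sponsor prefers to leave centre out, the SAP should state and justify that, and SAP 5.3 should say whether the 135 per group still includes an allowance for centre.

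The cost is about 5 degrees of freedom, or 10 with centre-by-time. Centre is already recorded as the stratification factor, so no new data are needed.

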## 5.4 Statistical framework

### 5.4.1 Hypothesis test

Primary outcomes will be determined by measuring the change in the average of measured frequencies between 500Hz and 4kHz between baseline and control 2 years after the operative implantation of tympanostomy tubes. The null hypothesis is that controls performed by the GP lead to poorer PTA results 2 years after implantation of tympanostomy tubes compared to those performed within the specialist health care system. The alternative hypothesis will be that the mean change in PTA of patients controlled by their GP is not inferior to the PTA of patients controlled in the specialist health care system.

The test will be performed at the two-sided 5% significance level. A difference between the two groups will be claimed if the null hypothesis is rejected (p-value less than 5%). Superiority of controls within the specialist health care system will be claimed if the two-sided p-value in the test comparing the change from baseline is less than 5% and if the effect goes in favor of controls performed within the specialist health care system.

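### The primary endpoint has two unranked analyses, a linear mixed model and a raw change-score t-test, and the mixed model as written forces one variance before surgery and at 2 years

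*Combined protocol and SAP*

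**What the plan says.** **Analyses.** SAP 8.1.2 plans an LMM "with the combination of time and treatment as fixed factors" at three levels (baseline, post-ENT, post-GP), with participant as the random factor, to compare PTA at 2 years. It states no residual covariance. The section then adds a second analysis: "We will also perform a t-test to compare the mean change in PTA after 2 years between GP controlled patients" and specialist-controlled patients. It does not say which of the two decides.

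**Children used.** SAP 8.1.3 keeps the baseline values of children lost to follow-up in the LMM and notes that these children do not affect the t-test.

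**Claims.** SAP 5.4.1 says "The test will be performed at the two-sided 5% significance level". Superiority of specialist follow-up is claimed "if the two-sided p-value in the test comparing the change from baseline is less than 5" per cent and the effect favours the specialists. The general rule for claiming a difference names no test, and neither does the non-inferiority hypothesis.

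**The SD.** SAP 5.3 sizes the trial for an "absolute difference in mean PTA between the groups of" 5 dB or more with SD 10 dB, in a passage about PTA at 2 years. The protocol (Number of participants) describes changes between two timepoints, improvements of 10 and 5 dB, and an "estimated standard deviation of 10dB in each group".

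**The concern.** Two tests of one endpoint, on different data and with different precision, can give different answers. With no ranking, the choice can be made after both results are known. For a trial whose message turns on whether an interval stays within 5 dB, this matters more than for a trial expecting a large effect.

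Two further points affect the width of that interval. First, the one claim rule that describes its test points most naturally to the less precise analysis. Second, a participant random effect with default residuals gives pre-operative and 2-year PTA the same variance. If surgery changes the spread of hearing levels, the pre-operative spread leaks into the standard error of the 2-year contrast, which is then too wide or too narrow.

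**Working it through.** **Inputs.** Two-sided 5% level (SAP 5.4.1). 5 dB difference, SD 10 dB, 95% power and 105 per group (SAP 5.3). Final target 135 per group (SAP 5.3). The documents give no correlation between baseline and 2-year PTA (ρ) and no visit-specific SDs (s0 before surgery, s1 at 2 years), so these are assumed below. The analysed number is also assumed: 135 × (1 − 0.20) = 108 per arm, using the original 20% dropout allowance.

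**1. The plan's figure.** n = 2(1.960 + 1.645)² × 10² / 5² = 104.0. The t-based version gives 104.9, so 105. The stated figure reproduces.

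**2. Precision of the two approaches.**
- Variance of change: s0² + s1² − 2ρ·s0·s1.
- Baseline-adjusted variance: s1²(1 − ρ²).
- Difference between them: (s0 − ρ·s1)², which is never negative.

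So the change score cannot beat a correctly specified adjusted analysis.

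**3. Power if 10 dB is the SD of PTA at each visit.** Here SD(change) = 10√(2(1 − ρ)) and SD(adjusted) = 10√(1 − ρ²). Noncentral t, 5 dB difference, 108 per arm:

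| ρ (assumed) | SD change | SD adjusted | Power, change t-test | Power, adjusted |
|---|---|---|---|---|
| 0.2 | 12.65 | 9.80 | 82% | 96% |
| 0.3 | 11.83 | 9.54 | 87% | 97% |
| 0.4 | 10.95 | 9.17 | 92% | 98% |
| 0.5 | 10.00 | 8.66 | 95.5% | 99% |
| 0.7 | 7.75 | 7.14 | 99.7% | 99.9% |

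The change test meets the SAP's 95% standard only from a correlation of about 0.5 upward.

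**4. Power if 10 dB is the SD of change.** The change t-test has 95.0% at 105 per arm and 95.5% at 108, whatever the SD of PTA itself.

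**5. Standard error of the LMM as written.** Let avg = (s0² + s1²)/2, cov = ρ·s0·s1 and b = cov/avg.
- Model SE = √(avg(1 − b²) × 2/n).
- True SE = √((s1² − 2b·cov + b²·s0²) × 2/n).

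With ρ = 0.3, n = 108 and SDs of 10 and 7 in either order: avg = 74.5, cov = 21, b = 0.282, model SE = 1.13.
- SD 10 then 7: true SE = √((49 − 11.84 + 7.95) × 2/108) = 0.91. The model SE is about 23% too wide.
- SD 7 then 10: true SE = √((100 − 11.84 + 3.89) × 2/108) = 1.31. The model SE is about 14% too narrow. One-sided error is 1 − Φ(1.96 × 0.863) ≈ 4.5% instead of 2.5%.

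In simulation at 105 per arm with SDs of 10 then 13, two-sided error was 8.1% to 8.6%. An unstructured covariance held 4.5% to 5.7% in every setting run.

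**6. Disagreement between the tests.** Non-inferiority is taken here as an upper 95% limit below the SAP's "5 dB as equivalence margin", an assumption because SAP 5.4.1 does not state the rule this way. With complete data, 108 per arm, SD 10 at both visits and ρ = 0.3, simulated verdicts differ in about 11% of trials when the true difference is 0, and in about 24% when it is 1.5 to 2 dB. At ρ = 0.5 the figures are about 4% and 15% to 19%. Under the p < 0.05 rule at 105 per arm with equal SDs, at least one of the two tests is significant in about 8% of trials with no true difference.

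**The case against.** The strongest reply is that only a label is missing. The LMM comes first and the t-test is introduced with an *also*, which reads naturally as supportive. Because the LMM shares one baseline level, post-GP minus post-ENT equals the difference between the two changes from baseline, so the wording of SAP 5.4.1 can be stretched to cover it. This has force. A reader might infer that every claim rests on the weaker test. The documents do not support that: only the specialist-superiority rule refers to a change-from-baseline test. What stands is that the SAP never says which analysis decides.

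A reader might also infer that the trial is underpowered. On the protocol's wording, where 10 dB describes change, it is not: the t-test keeps its stated power and is only less efficient than it could be. The lower powers follow from the SAP 5.3 wording combined with low correlations, and the SAP says that 135 followed a reassessment of dropout, so 108 may not be the right analysed number.

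Nor is the change test biased by regression to the mean. Randomization protects the contrast, and the cost is precision. Leaving out children without a 2-year visit is disclosed in SAP 8.1.3, and such children have no 2-year outcome in either analysis.

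On the LMM, the equal-variance constraint follows from default residuals; the SAP neither states nor relaxes it. Nothing in the documents says that spread rises after surgery. If it falls, the interval is too wide, which is conservative for non-inferiority.

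**Conclusion.** The concern holds in this form: two unranked analyses of the primary endpoint, non-inferiority tied to no named test, and an LMM that as written assumes equal variance at two visits separated by an operation intended to improve hearing.

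The efficiency ordering in step 2 is algebra and needs no assumption. The sizes do. The change test's power runs from about 82% to 99.7% over assumed correlations of 0.2 to 0.7 if 10 dB is the SD at each visit, and is 95% or slightly more if it is the SD of change. The LMM standard error is about 23% too wide or 14% too narrow for the assumed SD pairs, and the direction depends on which visit is more variable. With equal SDs the LMM is correct. The documents do not settle which case applies, so neither an inflated error rate nor a loss of power can be asserted for this trial. The point should be settled before unblinding; it does not invalidate the design.

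**What to change.** - In SAP 5.4.1 and 8.1.2, state that the single confirmatory estimate for every claim (non-inferiority, difference, specialist superiority) is the LMM contrast post-GP minus post-ENT at 2 years with its two-sided 95% CI.
- Label the change-score t-test as supportive, with no role in any claim.
- Fit the LMM with an unstructured 2x2 covariance, giving baseline and 2-year PTA separate variances, in place of a participant random intercept with default residuals.
- In SAP 5.3, state whether the 10 dB SD describes PTA at a visit or change in PTA, and reconcile this with the protocol.

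The cost is a few sentences of SAP wording, one covariance option in Stata or R, and one extra variance parameter. No new data are needed.
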